**BACKGROUND**

**In-Vitro Fertilisation (IVF) is common.** 5% of Australian births are now conceived by IVF. It is well established that pregnancy following IVF is associated with higher risk of maternal and perinatal complications than pregnancy where conception occurs naturally. There is emerging epidemiological evidence suggesting that Intra-Cytoplasmic Sperm Injection (ICSI) may be associated with an increased risk of congenital abnormalities, Autism Spectrum Disorder and other developmental abnormalities compared to (standard) IVF or natural conception. Analysis of existing data has, however, generated results on the risk of these adverse outcomes that are not consistent across studies.

**There are currently few published studies looking at population-wide school-age education and developmental outcomes among children following IVF conception with appropriate comparison between difficerent types of assisted reproductive technology (ART) and a control group representing natural conception (NC).** We will use record-linkage of existing administrative datasets to investigate the evidence of a causal relationship between relatively rare exposure of IVF (compared to natural conception, or ICSI compared to IVF) and the developmental and educational outcomes of primary school-aged children. Outcomes measures of primary interest are achievement assessed using the Australian Early Developmental Census (AEDC) and National Assessment, Literacy and Numeracy (NAPLAN) metrics.

**CAUSAL RESEARCH QUESTION**

***What are the causal effects of Invitro Ferilization (IVF) v Natural Conception (NC) and IVF with Intracytoplasmic Sperm Injection (ICSI) v conventional IVF on the school-age developmental and educational outcomes for children?***

P – All Mothers (and their babies) who gave birth in Victoria during the period 2005-2018

*Note: we intend to consider mothers, fathers and children part of the target population even if we know that they do not have outcomes data available (e.g. AEDC)*

I – Conception via (i) any IVF; (ii) IVF with ICSI.

C – Conception via (i) natural conception (excluding ovulation induction (OI) and intra-uterine insemination (IUI)); (ii) conventional IVF.

O – Developmental and educational outcomes – AEDC and NAPLAN (Grade 3) scores.

T – The nominal age at which children are measured for AEDC (foundation school year: 4-6 years of age) and NAPLAN (school year level 3: 7-9years of age) are typically measured.

**NULL HYPOTHESIS**

**The population distribution of school-aged developmental and educational outcomes for children conceived via conventional IVF or ICSI are the same as those of children born after natural conception.**

**DATA SOURCES**

1. Victorian Perinatal Data Collection
   1. Approximately 1,000,000 Victorian births between 2005-2018
   2. Routinely-collected data from the electronic Birthing Outcome System (BOS).
2. Major IVF providers in Victoria
   1. Cycle data from all pregnancies that resulted in a birth from each of the following IVF providers 2005-2018 (approximately **30,000 cycles):**
      1. Melbourne IVF
      2. Monash IVF
      3. City Fertility Centre
3. Australian Early Developmental Census
   1. Performed *every three years* across Australia. These data are collected by prep school teachers who conduct an observational assessment of every child in their first year of full-time primary school.
   2. Birth data to be linked with corresponding AEDC data from 2009 (unlikely to link with births in our study cohort), **2012, 2015, 2018.**
   3. **Five domains of assessment:**
      1. Physical health and wellbeing – looks at absence from school due to illness, independence with toileting, coordination, fine motor skills and physical ability to climb stairs, and other aspects.
      2. Social competence – assesses ability to get along with peers, respect for adults and others, curiosity about the world and eagerness to play and learn, willingness to help other children who are hurt or having difficulty with an activity and problem-solving day-to-day tasks.
      3. Emotional maturity – aims to identify impulsive or bullying behaviour, as well as the child’s ability to make decisions, be patient and attentive, share and wait their turn in games.
      4. Language and cognitive skills – assesses ability to use English effectively; listen and follow instructions in addition to more in-depth assessments of reading, writing and numeracy.
      5. Communication skills and general knowledge – looks at the child’s ability to tell a story, participate in imaginative play, communicate their own needs to their peers and to adults and assesses their knowledge about the world (eg. the seasons, types of fruit, different animals etc).
   4. From the teacher’s assessment, an individual score is calculated for each child. Outcome measures include *both* a **score** (out of 10) and a **centile** for each domain for every child. Centile scores are used to define:
      1. *developmentally “vulnerable” = <10^th^ centile (in any domain)*
      2. *developmentally “at risk” = 10-25^th^ centile (in any domain)*
      3. *developmentally “on track” = > 25^th^ centile (in any domain)*
4. National Program for Numeracy and Literacy Assessment (NAPLAN) – Victorian Data
   1. Annual school-based assessment
   2. Performed in school years 3, 5, 7, 9
   3. Four domains of assessment, each with a scaled **score** out of 1000, a “band” **category** (1-10 & 1-6 for grade 3) and a dichotomous **“**above or below” **minimum standard**.
      - *Reading*
      - *Writing*
      - *Language conventions (spelling, grammar and punctuation)*
      - *Numeracy*
      - *Overall score – overall academic ability (if data available)*

**DESCRIPTIVE ANALYSIS**

**1. Flow chart of study participants:**

[figure not shown]

**2. Population characteristics to be described:**

a) Overall cohort

b) Non-IVF cohort (naturally-conceived children) only

c) ART cohort overall (IVF, ICSI, IUI, OI)

d) IVF cohort only

e) ICSI cohort only

| **VARIABLE** | **DESCRIPTOR** |
| --- | --- |
| **Child baseline data** | |
| Sex | (% female) |
| Language Background Other Than English | (%) |
| Aboriginal / Torres Strait Islander | (%) |
| [*Mother born overseas*]  [*Father born overseas*]  Any parent born overseas | (%) |
| Birthweight | Mean and SD |
| Gestational age of delivery | Median and IQR |
| Plurality:  No. Twins  No. Triplets  No. Quads | Absolute numbers and % |
| Method of delivery | (% C/S) |
| **Maternal baseline data** |  |
| Maternal age | Median and IQR |
| Marital status:  Married/de facto  Single  Divorced  Widowed | (% of each category) |
| Level of maternal education:  Year 10 or below  High school  Trade/TAFE/diploma/certificate  Undergraduate Uni degree or above | (% of each category) |
| Maternal Occupation:  Senior management,  Other business manager, Tradesman/woman, clerks, sales and service staff,  Machine operators,  Not in paid work,  Not Stated/Unknown | (% of each category) |
| SEIFA (Socio-Economic Index for Areas) quintile:  1 (most disadvantaged)  2  3  4  5 (least disadvantaged) | (%) for each category |
| **Second parent baseline data** |  |
| Level of second parent education:  Level of maternal education  Year 10 or below  High school  Trade/TAFE/diploma/certificate  Undergraduate Uni degree or above | (% of each category) |
| Second Parent Occupation:  Senior management,  Other business manager, -Tradesman/woman, clerks, sales and service staff,  Machine operators,  Not in paid work,  Not Stated/Unknown | (% of each category) |
| **Childhood outcome data** |  |
| **AEDC** | |
| Individual score | Median (IQR) |
| Developmental vulnerability (<10^th^ in ≥2 domains) | % |
| **NAPLAN** |  |
| Scaled score | Median (IQR) |
| Z-score | Mean (SD) |
| Band category | N (%) |
| Binary – minimum standard | % |
| Public or private school | % (if data available) |

Numbers and characteristics of children for which NAPLAN outcome data was *not* matched or available will also be described given that NAPLAN is not compulsory.

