**3. Figures**

a) AEDC:

- Graphs will be generated to describe a) the proportion of developmentally vulnerable children (<10^th^ centile ≥2 domains) and b) the proportion of children ‘on track’ amongst the overall cohort, natural conception, overall ART (assisted reproduction), IVF-only and ICSI-only cohorts

b) NAPLAN:

- Graphs will be generated to describe a) the proportion of children in the lowest band category and b) the proportion of children classified as ‘below minimum standard’ amongst the overall cohort, natural conception, overall ART (assisted reproduction), IVF-only and ICSI-only cohorts
- Represent as box and whisker plot of test scores for each study population
- Use of z-scores standardised by year of test and year level – we will use whole of Australia national standards

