**STATISTICAL ANALYSIS**

**PART ONE – AEDC**

**Causal research question:** What is the causal effect of conception via IVF compared to natural conception on AEDC-defined outcomes for children?

**Exposure**: IVF conception.

**Primary outcome:** A score of <10^th^ centile in “2 or more” domains (Binary yes/no).

**Secondary outcomes:** A score in the lowest decile in each domain: 1) physical health and wellbeing, 2) social competence, 3) emotional maturity, 4) language and cognitive skills, and 5) communication skills and general knowledge.

**Inclusion criteria:** Children born in the study time period.

**Exclusion criteria:** Multiple pregnancies, known congential anomaly.

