**Causal Inference methodology**

| *The steps to* ***causal inference****:*   1. *Think carefully about the precise nature of the causal question to be addressed, usually around a currently humanly feasible intervention that we wish to apply to the whole of the target population, and compare the outcome (averaged over the whole of the target population) to the corresponding average outcome that occurs when no one in the target population gets the intervention;* 2. *Convert the causal question in Step 1 to a precise quantity to be estimated (a causal estimand), usually using the notation of the potential outcomes approach to causal inference.* 3. *At least state and, if possible, be rigorous and honest about the the assumptions (e.g. consistency, conditional exchangeability, positivity) under which the estimand in Step 2 can be identified from the data at hand;* 4. *Find (or develop!) estimation strategies (i.e. statistical methods) that are valid under the assumptions in Step 3. Apply these to the data in Step 3;* 5. *Use statistical tools to assess quantitatively the sensitivity of the results to plausible departures from the assumptions in Step 3.* |
| --- |

1. Develop a causal model using directed acyclic graphs (DAGs) to both identify and summarize causal pathways.
   1. Potential confounders – demographic and perinatal – will be determined by a quorum of specialists with expert knowledge:
      1. Childs age at assessment (continuous)
      2. Gender (binary)
      3. Birthweight centile (continuous or binary, eg < 10^th^ centile)
      4. Gestational age of delivery (continuous)
      5. Mode of delivery (categorical)
      6. Level of maternal education (categorical)
      7. Maternal age (continuous)
      8. SEIFA quintile (categorical)
      9. LBOTE (binary)
      10. ATSI (binary)

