**PART TWO – NAPLAN**

**Causal research question:** What are the NAPLAN-defined outcomes for children conceived via IVF vs those conceived naturally?

**Exposure:** IVF conception.

**Primary outcome:** Z score to be generated from our cohort using published mean and SD for national-scaled scores.

- Means and SD for each child will be scaled to the national score for the particular year that the child was assessed. The scaled score provided is overall, thus it is expected that children in Grade 3 will have lower average scores than those in Grade 5.

**Secondary outcomes:** Above or below minimum standard for each of the four domains (binary).

**Inclusion criteria:** Children born during the study time period.

**Exclusion criteria:** Multiple pregnancies, known congential anomaly.

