**PART THREE – ICSI ANALYSIS**

ICSI forms an important and growing proportion of IVF technique. Outcomes amongst this sub-population will be explored separately and subsequent to the analyses in Part One and Two.

**Causal research question:** What is the causal effect of conception via ICSI compared to non-ICSI (conventional) IVF compared to natural conception on AEDC and NAPLAN outcomes for children?

**Exposure**: IVF with ICSI

**Primary outcome: *AEDC*** A score of <10^th^ centile in “2 or more” domains (Binary yes/no). ***NAPLAN***: Z score to be generated from our cohort using published mean and SD for national-scaled scores.

**Secondary outcomes:** ***AEDC*** A score in the lowest decile in each domain: 1) physical health and wellbeing, 2) social competence, 3) emotional maturity, 4) language and cognitive skills, and 5) communication skills and general knowledge. ***NAPLAN:*** Above or below minimum standard for each of the four domains (binary).

**Inclusion criteria:** Children born in the study time period.

**Exclusion criteria:** Multiple pregnancies, known congential anomaly.

*If there* ***ARE*** *differences in developmental and educational outcomes between ICSI and conventional IVF cohorts, we propose that this will be considered and reported as a primary finding since we have stated this sequential planned analysis a priori.*

The same methodology of causal inference, detailed in Part One and Two, will be employed for this analysis.

*Again, this analysis will focus on the* ***total effect*** *of ICSI conception adjusted for common cause confounders.*

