**Types of nodes (variables) in the above DAG**

**Common-cause confounders of the causal effect of the primary exposure (IVF) on the primary outcome (NAPLAN) [arrows from these variables to both IVF and NAPLAN]:** SEIFA, LBOTE, Maternal education, ATSI. Adjust all analyses (via IPW) for these as potential confounders.

**Mediators of the causal effect of** **the causal effect of the primary exposure (IVF) on the primary outcome (NAPLAN) [arrow from IVF to this variable, and then from this variable to NAPLAN, so they are “on the causal pathway”]:** CS, LBW, Prematurity (PTB), DevelopDelay.

**Variables that are common-cause confounders of the causal effect of the exposure (IVF) on one or more mediators:** Male SubFert and Female SubFert (confounds IVF and Prematurity), Maternal age (confounds IVF and all of CS, LBW and Prematurity).

**Variables that are common-cause confounders of mediators or causes of mediators (but are not mediators themselves):** Obesity, Maternal age.

**Mediators that common-cause confound the causal effect of another mediator on the outcome (NAPLAN) and are therefore “Exposure-Induced Mediator-Outcome Confounders” (EIMOC’s):** LBW (on Prematurity), Prematurity (on DevelopDelay).

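### The plan's DAG makes subfertility a confounder of IVF v natural conception, but Parts One and Two neither firmly adjust for it, specify a sensitivity analysis for it, nor use the OI/IUI births in any contrast

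*SAP*

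**What the plan says.** **Comparator and contrasts.** Under CAUSAL RESEARCH QUESTION the first comparator is "natural conception (excluding ovulation induction (OI) and intra-uterine insemination (IUI"). The inferential questions are:
- Part One: "What is the causal effect of conception via IVF compared to natural conception on AEDC-defined outcomes for children"
- Part Two: "What are the NAPLAN-defined outcomes for children conceived via IVF vs those conceived naturally"
- Part Three: "What is the causal effect of conception via ICSI compared to non-ICSI (conventional) IVF compared to natural conception"

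**OI/IUI.** These births appear in the descriptive table only inside "c) ART cohort overall (IVF, ICSI, IUI, OI"). In the figures they appear only within the ART group among "overall ART (assisted reproduction), IVF-only and ICSI-only cohorts". They are never shown as a group of their own.

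**Subfertility.** Part Four, on types of nodes, lists "Male SubFert and Female SubFert (confounds IVF and Prematurity") and makes prematurity a mediator to NAPLAN. The same section's common-cause set for IVF and NAPLAN is SEIFA, LBOTE, maternal education and ATSI. The next section, Proposed Causal Mediation Analyses, adds maternal age, male and female subfertility and multiple pregnancy to the variables it considers safe to adjust for in every analysis. The starting propensity list in Part One has no subfertility item, but the SAP says the list is still to be finalised.

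**Sensitivity.** Step 5 of the causal-inference box in Part One reads: "Use statistical tools to assess quantitatively the sensitivity of the results to plausible departures from the assumptions in Step 3". Conditional exchangeability is one of the Step 3 assumptions.

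**The concern.** The primary analyses in Parts One and Two aim at the total effect of IVF, adjusted for common causes. If subfertility is a common cause and is not adjusted for, the IVF v NC estimate mixes the effect of IVF with that of the parents' subfertility. The SAP expects differences to be highly significant because of the cohort size, so precision gives no protection: a purely confounded difference could be significant and be reported as a causal effect of IVF.

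Two safeguards were within reach. One is the sensitivity assessment that the SAP itself names. The other is a comparison with children conceived by fertility treatment other than IVF. Neither is specified.

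**Working it through.** The SAP gives no sample size, power or OI/IUI count, so there is no figure of its own to reproduce. The first three steps compare sections; the last two are illustrative arithmetic.

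**1. Is subfertility a confounder by the plan's own account?** The node classification gives subfertility → IVF, subfertility → prematurity and prematurity → NAPLAN. The path IVF ← subfertility → prematurity → NAPLAN is therefore an open back-door path. Adjusting for gestational age, which is on the starting list, would block this path. It would also remove the part of the total effect mediated by prematurity, so it is no substitute. The SAP's argument that obesity can be left out also assumes adjustment for female subfertility.

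**2. Is it adjusted for?**
- Part One starting propensity list: absent, list provisional.
- Part Four common-cause set: absent.
- Part Four, Proposed Causal Mediation Analyses: present, for all analyses. The SAP expects the mediation work to be a separate project.
- DATA SOURCES: the perinatal collection, IVF-provider cycle data, AEDC and NAPLAN. None is said to record subfertility for natural conceptions.

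If subfertility were known only through IVF records, its missingness would follow exposure. Imputation would have little to learn from, a missing-indicator term would nearly identify the NC group, and overlap would be doubtful. Adjustment may therefore not be feasible.

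**3. Is Step 5 put into operation?** The numbered steps after the box are the DAG, imputation, weights and regression. Part Two reuses the first three with its own regression section, and Part Three reuses the methods of both. No sensitivity analysis for exchangeability appears.

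**4. Possible size of the bias.** Bias = g × (p1 − p0), where g is the effect of subfertility on the outcome and p1, p0 are its prevalence in IVF and NC. Assumed pairs (p1, p0): 0.95, 0.05; 0.90, 0.10; 0.70, 0.15. The differences are 0.90, 0.80 and 0.55.
- g = 0.1 SD: bias 0.09, 0.08, 0.055 SD.
- g = 0.2 SD: bias 0.18, 0.16, 0.11 SD.
- g needed for a spurious 0.1 SD: 0.1/0.90 = 0.11, 0.1/0.80 = 0.125, 0.1/0.55 = 0.18 SD.
- AEDC, assumed baseline risk 10% and subfertility risk ratio 1.25: risk-difference bias = 0.10 × 0.25 × (p1 − p0), which is 1.4 to 2.3 percentage points. The spurious risk ratio runs from 1.175/1.0375 = 1.13 to 1.2375/1.0125 = 1.22.

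**5. What an IVF v OI/IUI contrast could show.** SE = √(1/n_OI + 1/n_IVF) in SD units, unweighted, with n_IVF assumed to be 11,000. The difference detectable with 80% power at two-sided 5% is 2.8 × SE.
- n_OI = 1,000: SE 0.033, detectable 0.092 SD.
- n_OI = 3,000: SE 0.0206, detectable 0.058 SD.
- n_OI = 6,000: SE 0.016, detectable 0.045 SD.

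With 5,000 to 10,000 IVF children instead, power for 0.1 SD is 57–59% with 500 OI/IUI children, 82–85% with 1,000 and 97–98% with 2,000. For a binary outcome of 10% v 12.5%, power with the same three OI/IUI numbers is 43–45%, 65–69% and 85–90%. Weighting lowers all of these. As an upper case, a 1.9-fold inflation of the SE would move the detectable differences above (0.045 to 0.092) to about 0.09 to 0.17 SD. AEDC numbers would also be smaller, since that census runs every three years.

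**The case against.** The strongest reply is that the SAP does address subfertility: Part Four names it for adjustment, and the propensity list is open until back-door paths have been considered. That stands in part. A reader might infer that the plan **cannot** separate IVF from subfertility; the text supports only that, as written, it does not.

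A reader might also infer that subfertility is unrecorded in about 97% of births, from 30,000 cycles against 1,000,000 births. The SAP gives no variable list for the perinatal collection, so this cannot be established. Likewise, the Step 5 assessment is not specified; nothing shows that it will not be carried out.

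It can be said that excluding OI/IUI gives a clean comparator that fits the stated question, and that a further contrast is a matter of preference. The exclusion is indeed sound, and the point does not ask for it to be reversed. But an extra contrast is a direct response to a confounder that the plan itself names and may be unable to measure.

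Finally, OI/IUI ascertainment is uncertain. Removing these births from NC and counting them in ART presupposes that they can be identified at least in part. However, the only treatment source named is three IVF providers, so some may be missed or counted as natural conceptions. OI/IUI parents may also be less severely subfertile. Both limits stand.

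**Conclusion.** The point holds as an internal inconsistency with a consequence for interpretation. By the SAP's own classification, subfertility confounds the total effect of IVF v NC. Its sections disagree on whether to adjust for it, no source is said to record it in natural conceptions, and the quantitative sensitivity step has no content. Under the assumed prevalences, a subfertility effect of 0.11 to 0.18 SD would by itself produce the SAP's 0.1 SD difference. These are illustrations; the SAP supplies neither the prevalences nor the effect.

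An IVF v OI/IUI contrast would help but would not settle the matter. A reader might infer a strict rule: attribute a difference to IVF only if it persists at similar size against OI/IUI. The precision does not support that. With 1,000 OI/IUI children the 95% half-width is about 1.96 × 0.033 = 0.065 SD before weighting, so failure to persist could be noise. The 1,000 to 6,000 OI/IUI and 11,000 IVF children are assumptions.

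**What to change.** 1. Reconcile the Part One covariate list, the Part Four common-cause set and the Part Four list for all analyses on subfertility. State whether any source records it for natural conceptions and, if none does, that it is treated as unmeasured.
2. Add to Parts One and Two a pre-specified secondary (sensitivity) contrast of IVF v OI/IUI, with the same outcomes, covariates and estimator. Report the number of OI/IUI births and how they were ascertained.
3. Give Step 5 content: a quantitative bias analysis for unmeasured subfertility, for example an E-value or the formula bias = subfertility effect × prevalence difference over a stated range.
4. Interpret the OI/IUI contrast by its estimate and confidence interval, set beside IVF v NC. Describe an IVF v NC difference as a possible joint effect of IVF and subfertility unless both the contrast and the bias analysis support an effect specific to IVF.

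The cost is SAP wording, a further run of the planned code and a short bias calculation, plus a check of how completely OI/IUI births are captured. The contrast will be less precise than IVF v NC, especially for AEDC, and will leave some confounding.
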